**Fig. 1 Fig1:**
[figure not shown]
Timeline cluster diagram of the study

### Sample size

Power calculations are conducted around the principle of observing “statistically significant” differences between study arms. “Statistical significance”, however, is not a concept typically used in Bayesian analyses, nor is it the appropriate consideration here for determining the effectiveness of our intervention. We conduct instead an “assurance analysis” to determine the probability of estimating an effect size to within a given degree of certainty with the data generated by the trial [13]. This has a more natural interpretation and allows us to take into account our prior uncertainty over effect size. In this case, the appropriate level of certainty is that which ensures a negligible probability of the sign of the effect (i.e. positive or negative) being incorrectly inferred. Given that the assurance calculations are intractable mathematically, we simulate a large number of trials and analyses.

Overall, 132 SMEs are planned to participate in the trial, and they will be allocated equally between arms, i.e. 33 per trial arm. We aim to interview a random sample of ten employees per SME. For the purposes of the design evaluation and generation of simulation data we consider informative priors (similar to prior beliefs about effect size in frequentist power calculations albeit with uncertainty), as distinct from the analysis priors to be used in the analysis stage and model estimation. The treatment effects for the 50 and 100% incentive arms were modelled as 1.3 ± 0.1 and 1.5 ± 0.1, respectively. The baseline was assumed to be between 10 and 50%. For cRCTs such as this, the variance can be partitioned into three components: between cluster, within cluster-between period, and within-individual. The ‘power’ of the trial design depends on the intra-cluster correlation coefficients (ICC) (both between and within periods) and the cluster autocorrelation (CAC), which captures how similar cluster outcomes are over time. We also assumed the within-period ICC (the proportion of variance attributable to the cluster level) would lie between 0.02 and 0.1 uniformly and the CAC would be uniformly distributed between 0.75 and 1. Finally, we simulated the measurement effect to be, as a relative risk ratio, between 0.9 and 1.1.

Based on the design of the trial, we determined the probability that there would be at least a 95% posterior probability that each treatment effect (as an odds ratio) would be > 1 and hence that the absolute difference between the treatment effects would be > 0. The respective probabilities for the 50 and 100% treatment conditions were 70 and 79%, and the probability for the difference was > 99%. Therefore, we consider the sample size to be sufficient. For comparison, a “classical” power calculation with 5% type I error probability and values at the mean values of the parameters stated above for a two-arm trial gives a power of 68 and 92% for the two treatment conditions respectively [14].

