### Analysis plan

#### Quantitative outcomes

Descriptive data for continuous measures will be presented as means±SD. Descriptive data for categorical measures will be presented as numbers and percentages.

We will conduct a Bayesian constrained regression-based analysis of the trial data that incorporates the possibility of an additive measurement effect and time effects. The constrained regression analysis assumes that there are no systematic differences between clusters at baseline and hence no covariates are included in the model, which reflects the constrained randomisation procedure described above. The model includes treatment effects for each treatment condition, an effect for if the cluster has been measured prior to the time of observation, a cluster random effect, fixed effects for each time point, and a random cluster by time point interaction. We will use a log-binomial model as the interest lies in relative risk effects, which this model’s parameters provide. The full specification is provided in the Additional file 6.

We opt for a Bayesian approach to allow for the incorporation of prior uncertainty, facilitate computation of a complex hierarchical model, and provide a more intuitive interpretation of parameter estimates, which naturally incorporate into decision analyses such as economic evaluations. We will assign “weakly informative” priors to the model parameters, which provide little information on the parameter value but ensure regularisation of the model and facilitate computation. In particular, we will use normal distributions with a standard deviation of ten for parameters in the linear predictor and half-standard Cauchy priors for the hyper parameter variance terms [13, 14].

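### The scale of the assumed effects 1.3 and 1.5 is not stated, and the assurances of 70% and 79% are reproduced neither as relative risks nor as odds ratios

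*Protocol article*

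**What the plan says.** All references are to the protocol article.

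- **Sample size, effects.** "The treatment effects for the 50 and 100% incentive arms were modelled as 1.3 ± 0.1 and 1.5 ± 0.1, respectively". No scale is given in that sentence.
- **Sample size, measurement effect.** Here a scale is given: "we simulated the measurement effect to be, as a relative risk ratio, between 0.9 and 1.1".
- **Sample size, criterion and result.** The quantity reported is the probability of "at least a 95% posterior probability that each treatment effect (as an odds ratio) would be > 1". The article gives 70% for the 50% incentive and 79% for the 100% incentive, and concludes that the sample size is sufficient. For comparison it reports classical powers of 68% and 92%.
- **Analysis plan, Quantitative outcomes.** "We will use a log-binomial model as the interest lies in relative risk effects". The model has a treatment effect for each incentive level, time effects, an effect of prior measurement, a cluster random effect and a cluster-by-time random effect. Priors on the linear predictor are normal with a standard deviation of ten.

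**The concern.** Three statements about scale do not fit together. The assumed effects have none, the assurance criterion is worded for odds ratios, and the planned model estimates relative risks. With a baseline of 10 to 50% the two scales diverge. From 30%, multipliers of 1.3 and 1.5 lead to 39% and 45% as relative risks, but only to about 36% and 39% as odds ratios. A reader cannot tell which improvement the trial was sized to detect.

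The reported pair also looks odd in itself. Both incentive arms have the same number of SMEs, the same controls and the same correlation structure, yet moving the effect from 1.3 to 1.5 adds only 9 points of assurance. These two figures support the article's statement that the sample size is sufficient, so it matters whether they follow from the stated inputs.

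**Working it through.** **Inputs (Sample size section).**
- Clusters: "132 SMEs are planned to participate in the trial, and they will be allocated equally between arms, i.e. 33 per trial arm".
- Cluster size: "We aim to interview a random sample of ten employees per SME".
- Baseline: "The baseline was assumed to be between 10 and 50" per cent, taken here as uniform.
- Correlation: the within-period ICC "would lie between 0.02 and 0.1 uniformly and the CAC would be uniformly distributed between 0.75 and 1".
- Measurement effect: relative risk 0.9 to 1.1, taken as uniform.
- Effects: 1.3 ± 0.1 and 1.5 ± 0.1, with ±0.1 read either as a standard deviation (SD) or as a uniform half-width.
- Criterion: posterior probability of at least 95% that the effect exceeds 1. Under near-flat priors this is z > 1.645.

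**Step 1: hand check at the middle values** (baseline 0.30, ICC 0.06, 33 against 33 SMEs, follow-up data only).

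Design effect = 1 + (10 − 1) × 0.06 = 1.54. Effective n per arm = 330 / 1.54 = 214.3.

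As relative risks, p = 0.39 and 0.45, and Var(log RR) = [(1 − p)/p + 0.70/0.30] / 214.3:
- 50% arm: (1.564 + 2.333)/214.3 = 0.01819, SE 0.1349. z = 0.2624/0.1349 = 1.945. Φ(1.945 − 1.645) = 62%.
- 100% arm: (1.222 + 2.333)/214.3 = 0.01659, SE 0.1288. z = 0.4055/0.1288 = 3.148. Φ(1.503) = 93%.

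As odds ratios, the baseline odds are 0.30/0.70 = 0.4286. Then p = 0.5571/1.5571 = 0.358 and 0.6429/1.6429 = 0.391, and Var(log OR) = [1/(p(1 − p)) + 1/0.21] / 214.3:
- 50% arm: (4.352 + 4.762)/214.3 = 0.04253, SE 0.2062. z = 0.2624/0.2062 = 1.272. Φ(−0.373) = 35%.
- 100% arm: (4.198 + 4.762)/214.3 = 0.04181, SE 0.2045. z = 0.4055/0.2045 = 1.983. Φ(0.338) = 63%.

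**Step 2: average over the stated ranges with the planned terms.** Generalised least squares (GLS) on cluster-period means, with a common baseline, a time effect, a measurement effect, two treatment effects, and cluster and cluster-by-period correlation from the ICC and CAC. The second control arm has no baseline data.

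| Scale of 1.3 and 1.5 | Calculation | 50% arm | 100% arm | Gap (points) |
|---|---|---|---|---|
| Stated in the article | – | 70% | 79% | 9 |
| Relative risk | GLS, ±0.1 as SD | 61.7% | 87.1% | 25.4 |
| Relative risk | GLS, ±0.1 as uniform half-width | 63.9% | 88.0% | 24.1 |
| Relative risk | direct simulation of 4,000 binary-data trials | 62.6% | 86.7% | 24.1 |
| Odds ratio | GLS, ±0.1 as SD | 36.9% | 63.5% | 26.6 |
| Odds ratio | GLS, ±0.1 as uniform half-width | 37.2% | 64.5% | 27.3 |
| Odds ratio | direct simulation of 4,000 binary-data trials | 37.4% | 62.9% | 25.5 |

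**Step 3: look for a setting that gives 70% and 79%.** None of those tried does.
- Relative risk, measurement term dropped: 68.9% and 92.0%.
- Relative risk, 33 against 66 SMEs with baseline adjustment: 69.9% and 92.1%.
- Relative risk, two-sided 5%, no baseline data: 48.6% and 78.5%.
- Relative risk, prior three times wider (SD 0.3 on the log scale): 53.8% and 70.4%.
- Odds ratio, ICC zero and measurement term dropped: 53.4% and 82.8%. This was the highest 50%-arm figure on that scale.

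Settings that bring one arm to its stated figure move the other well away from its own.

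**Step 4: the gap.** The article's classical pair differs by 92 − 68 = 24 points, close to the gaps in Step 2. This is only an indication, because that pair was not reproduced either (about 50% and 90% at the middle values, relative-risk scale, two-sided). Averaging over the baseline does narrow the gap. In the full model on the relative-risk scale, though, it goes from 92.5 − 64.4 = 28 points at a fixed 30% baseline to about 25 points, not to 9.

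**The case against.** **The criterion is the same on both scales.** An odds ratio exceeds 1 exactly when the relative risk does. This stands: the odds-ratio wording does not change what counts as success. What remains open is the scale on which 1.3 and 1.5 entered the simulation.

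**The relative-risk reading has better textual support.** The measurement effect is a relative risk and the planned model is log-binomial. This also stands. A reader might infer from the odds-ratio wording that the lower-incentive comparison has little more than a one-in-three chance of meeting its criterion. The article does not support that as a finding: no sentence says that 1.3 was generated as an odds ratio, so the 37% is conditional on the less likely reading.

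**On the relative-risk scale the error is modest and mixed.** The average over the two arms hardly moves: (70 + 79)/2 = 74.5% stated, (61.7 + 87.1)/2 = 74.4% here. The article sets no minimum assurance, so no stated threshold is crossed. This stands as well, and it rules out inferring that the trial is too small.

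**The authors' model was not run.** Theirs is a Bayesian hierarchical model specified in an additional file not shown. The figures here use a normal approximation with the ICC and CAC treated as known, and they depend on the assumed prior shapes. Across wider variants on the relative-risk scale, the 50% arm ranged from 52 to 72% and the 100% arm from 72 to 94%, so each stated figure taken alone lies within reach. The pair together does not. Estimating the variance components would be expected to lower assurance, which would not explain a 50%-arm figure above these results.

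**Conclusion.** The point holds as a reporting and arithmetic fault. The scale of the assumed effects is missing, the odds-ratio wording does not match the relative-risk analysis, and the pair 70% and 79% does not follow from the stated inputs on either scale.

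- **If relative risks:** the 50% arm is overstated by about 6 to 9 points and the 100% arm understated by about 7 to 9.
- **If odds ratios:** both are overstated, by about 33 and 15 to 16 points.
- **Gap between arms:** about 25 points in the main runs, against the 9 reported. A prior three times wider than stated still left about 17 on the relative-risk scale (70.4 − 53.8).

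These sizes assume a uniform baseline, ±0.1 as an SD or uniform half-width, near-flat priors, a normal approximation and known correlation parameters. I am confident that the pair is not reproduced and less so about the exact replacement values, which only the authors' own simulation can supply.

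**What to change.** 1. State in the Sample size section the scale on which 1.3 and 1.5 were simulated, what ±0.1 denotes, and the distribution used for the baseline.
2. Align the assurance criterion with the relative-risk analysis: remove the odds-ratio parenthesis or justify it.
3. Re-run the assurance with the model and priors of the Quantitative outcomes section, keeping the measurement effect as an estimated term, and replace 70% and 79% with the results.
4. Reword the statement that the sample size is sufficient so that it rests on the new figures.

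The cost is a re-run of an existing simulation and a few corrected sentences. Neither the design nor the number of SMEs has to change.

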This study provides a unique opportunity to build the evidence for incentives to improve employee health and might help in identifying the financial ‘tipping point’ for employers to engage in improving the health and wellbeing of their employees. It will also build further understanding of the barriers and enablers for effective interventions aimed at employees. The intervention was designed and the research team was commissioned to carry out an independent evaluation, combining three interrelated aspects:Recruitment evaluation (to explore why some SMEs remained ‘unconverted’ and did not signed up to the trial)Impact evaluation (to systematically measure the change in the organisation behaviour) andProcess evaluation (to understand how changes take place or why they do not occur).

This work can inform national policy regarding the effectiveness (or otherwise) of financial incentives and discussions about wider roll-out.

The aim is to evaluate the effectiveness of wellbeing financial incentives to SMEs in the West Midlands, UK. This primarily is to establish whether SMEs will improve their health and wellbeing offer and achieve higher employee awareness and participation in response to a financial wellbeing incentive. The evaluation also aims to assess whether financial incentives help and motivate SMEs overcome barriers when aiming to improve their wellbeing of their employees.

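### The > 99% probability given for the difference between the 100% and 50% incentive effects is wrong as an assurance for that contrast; the stated inputs give roughly 20% to 40%

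*Protocol article*

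**What the plan says.** All the inputs are in the Sample size section of the protocol article. On numbers: "Overall, 132 SMEs are planned to participate in the trial, and they will be allocated equally between arms, i.e. 33 per trial arm", and "We aim to interview a random sample of ten employees per SME". On effects: "The treatment effects for the 50 and 100% incentive arms were modelled as 1.3 ± 0.1 and 1.5 ± 0.1, respectively". That sentence gives neither the scale nor the meaning of ±0.1.

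Success is defined as a posterior probability of at least 95% that each treatment effect, as an odds ratio, exceeds 1, "hence that the absolute difference between the treatment effects would be > 0". The result is: "The respective probabilities for the 50 and 100% treatment conditions were 70 and 79%, and the probability for the difference was > 99" per cent. The next sentence concludes that the sample size is sufficient.

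The Background says that the study "might help in identifying the financial ‘tipping point’ for employers to engage in improving the health and wellbeing of their employees", and notes that varying degrees of incentive have not been explored before. The Analysis plan uses a log-binomial model because interest lies in relative risks.

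**The concern.** Three probabilities are offered as the basis for sufficiency, and the hardest of the three contrasts receives by far the highest one. The two incentive arms are as large as each control arm, and their assumed effects differ by a ratio of only 1.15, against 1.3 and 1.5 versus control. Near-certainty for the small contrast beside 70% and 79% for the larger ones is out of order.

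The linking logic also fails: both effects can exceed 1 and be equal.

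At stake is how the comparison of incentive levels will be read. Someone told that it had more than 99% assurance could take an inconclusive result as evidence that half the money does as well.

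**Working it through.** **Inputs.** From Sample size: 33 SMEs per arm; 10 employees per SME; effects 1.3 ± 0.1 and 1.5 ± 0.1; "The baseline was assumed to be between 10 and 50" per cent (taken as uniform, mean 30%); a within-period ICC that "would lie between 0.02 and 0.1 uniformly" (mean 0.06); cluster autocorrelation uniform on 0.75 to 1 (mean 0.875); measurement effect as a relative risk of 0.9 to 1.1. From Participant timeline: baseline data in three arms only. With weak analysis priors, a posterior probability of at least 95% corresponds approximately to estimate/SE > 1.645.

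**1. The article's own figures.** For each draw from the design priors, the SEs come from the generalised least squares information matrix of the described model (period effect, prior-measurement effect, two treatment effects, cluster and cluster-by-period variance). Assurance is the mean of Φ(log effect/SE − 1.645).

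| Scale of 1.3 and 1.5 | 50% arm | 100% arm | 100% vs 50% |
|---|---|---|---|
| Stated | 70% | 79% | > 99% |
| RR, ±0.1 as SD | 62% | 87% | 41% |
| OR, ±0.1 as SD | 37% | 64% | 21% |

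The stated pair 70/79% is not reproduced jointly. On the RR scale without the measurement-effect term the 50% arm reaches 70%, but the 100% arm then reaches 92%. The classical 68/92% is not matched jointly either: RR with baseline adjustment gives 55/93% two-sided and 67/96% one-sided.

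For the contrast, reading ±0.1 as an SD of 0.1, an SD of 0.05, a uniform range or a log-scale SD, or fixing the effects, gives 41% to 42% (RR) and 18% to 23% (OR). With effects at 1.3 and 1.5 and the most favourable corner of the ranges (baseline 50%, ICC 0.02, autocorrelation 1), it is 83% (RR) or 21% (OR).

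**2. At the mean values, RR scale.** log(1.5/1.3) = 0.143; SE = 0.107; z = 1.335; Φ(1.335 − 1.645) = 38%.

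**3. A check without the model.** Compare 330 with 330 employees at follow-up.
- RR, 30% baseline: 39% vs 45%. The design effect is 1 + 9 × 0.06 = 1.54, so effective n = 330/1.54 = 214. SE = √[(0.39×0.61 + 0.45×0.55)/214] = 0.048; Φ(0.06/0.048 − 1.645) ≈ 35%. With no clustering at all it is 47%.
- RR, 50% baseline, no clustering: 65% vs 75%, giving 88%.
- OR, 30% baseline: 35.8% vs 39.1%, giving 18%. With no clustering, no baseline tried from 10% to 50% exceeds 23%.

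**4. Coherence with 70% and 79%, at the mean effects.**
- 70% implies SE = log(1.3)/(1.645 + 0.524) = 0.121.
- 79% implies SE = log(1.5)/(1.645 + 0.806) = 0.165.
- 99% for the contrast needs SE = 0.143/(1.645 + 2.326) = 0.036.
- The correlation required between the two estimates is (0.121² + 0.165² − 0.036²)/(2 × 0.121 × 0.165) = 1.02 with unrounded SEs, which cannot occur.
- Perfect correlation gives SE = 0.165 − 0.121 = 0.044 and at most 94%. The design gives a correlation of about 0.53 to 0.63. At 0.5 to 0.65 the contrast has 25% to 30%.

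**5. What the priors allow.** If ±0.1 is an SD and the draws are independent, the true 100% effect exceeds the true 50% effect with probability Φ(0.2/√0.02) = 92%. That is the ceiling on assurance at any sample size. With an SD of 0.05, or a uniform range, the ordering holds in 99.8% or all draws, but that ordering is assumed at the outset and is not something the trial would show.

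**The case against.** The simulation code and the full model (Additional file 6) are not shown, and the approximation does not reproduce the 70/79% beside the disputed figure. That stands. It rules out writing 40% in as the replacement; only a range of about 20% to 40% and a request to re-run are supported. It does not rescue > 99%, because step 3 does without the model and step 4 uses only the article's own probabilities and mean effects.

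If *absolute difference > 0* means magnitude, > 99% is true. That also stands, so a reader who calls the number flatly impossible goes too far: the text does not settle the meaning. On that reading, however, the criterion is met in every simulation and cannot support sufficiency.

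A reader might infer that the contrast must fall below the weaker arm's 70% as a matter of logic. Strictly it need not, since highly correlated estimates would shrink its SE; the cap from the stated figures is 94%.

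A reader might also infer that the main question is underpowered. The documents do not support this. The hypothesis under Interventions and the aim under Outcome measures concern an incentive against none, the tipping-point remark is tentative, and no equivalence claim is made.

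Finally, a reader might conclude that a larger trial would deliver 99%. At fixed mean effects, 33 × (3.971/1.335)² ≈ 292 SMEs per arm would do so, but that is power, not assurance. With ±0.1 as an SD, the same size gives about 76% (RR), and the 92% ceiling puts 99% out of reach.

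**Conclusion.** Wrong as written. As an assurance that the 100% incentive will be shown to outperform the 50% incentive, > 99% is contradicted by the article's own inputs. The supported size is about 20% (odds ratios) to 40% (relative risks), or 25% to 30% if 70% and 79% are accepted. These rest on a normal approximation, a uniform baseline proportion and independent effect draws.

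The inference from both effects exceeding 1 to a positive difference is invalid on any reading. The 70% and 79% are not shown to be wrong, but they could not be reproduced together and should not carry the sufficiency statement unchecked. The fault is in the stated justification for a contrast that is not named as primary; design, randomisation, outcome and analysis model are untouched.

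**What to change.** 1. State whether 1.3 and 1.5 are odds ratios or relative risks, and whether ±0.1 is an SD, an interval or a range.
2. Re-run the existing simulation for all three probabilities. Define the third as the probability that the posterior probability of the 100% effect exceeding the 50% effect is at least 0.95.
3. Replace > 99% with that result and delete the *and hence* link.
4. Rest the sufficiency statement only on the re-run arm-versus-control figures.
5. Add that the 100% versus 50% contrast will be imprecise, so an inconclusive result is not evidence of equal effect.

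The cost is one re-run and one corrected paragraph. The contrast's figure will fall well below the one printed, and the arm figures may change. No extra SMEs are needed.

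### The classical powers of 68% and 92% cannot both come from one calculation at the stated mean values, so at least one is wrong

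*Protocol article*

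**What the plan says.** The Sample size section of the protocol article plans 132 SMEs in four arms: "they will be allocated equally between arms, i.e. 33 per trial arm". On cluster size it says "We aim to interview a random sample of ten employees per SME". The other design inputs are:

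- Effects: "The treatment effects for the 50 and 100% incentive arms were modelled as 1.3 ± 0.1 and 1.5 ± 0.1, respectively".
- Control rate: "The baseline was assumed to be between 10 and 50" per cent.
- Within-period ICC: it "would lie between 0.02 and 0.1 uniformly".
- Cluster autocorrelation (CAC): uniform between 0.75 and 1.

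The section reports assurance probabilities of 70% (50% arm), 79% (100% arm) and over 99% (the difference), and judges the sample size sufficient. It then adds that a classical calculation at 5% type I error and the mean parameter values "for a two-arm trial gives a power of 68 and 92% for the two treatment conditions respectively". It does not say whether the 5% is one- or two-sided, whether baseline data are used, or which control SMEs enter.

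The effect scale is not uniform. The assurance criterion refers to an odds ratio, while the Analysis plan (Quantitative outcomes) says "We will use a log-binomial model as the interest lies in relative risk effects".

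**The concern.** Both classical powers are presented as results of one calculation. Between the two comparisons only the effect size changes, 1.3 in one and 1.5 in the other. Once one power is given, the other is nearly determined, and 68% does not sit with 92%.

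The assurance figures come from simulation and a reader of the article cannot check them by hand. The classical pair can be checked. It stands directly after the statement that the sample size is sufficient, and its 68% looks like confirmation of the 70% assurance for the lower incentive. If 68% is the wrong figure, that apparent agreement is lost for the 50% arm, and a null result there would be read against an inflated power. If 92% is the wrong figure, the 100% arm is slightly undersold.

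**Working it through.** **Inputs.** All are from Sample size, taken at mid-range as the section says: k = 33 SMEs per arm, m = 10 employees, control rate 30%, ICC 0.06, CAC 0.875. Read as relative risks, the effects give 0.30 × 1.3 = 39% and 0.30 × 1.5 = 45%.

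**Step 1: can the pair arise at all?** Power is approximately Φ(z − c), where z is the standardised effect and c = 1.960 (two-sided 5%) or 1.645 (one-sided 5%). Powers of 68% and 92% correspond to z − c = 0.468 and 1.405.

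- Two-sided: (1.960 + 1.405) / (1.960 + 0.468) = 3.365 / 2.428 = 1.39.
- One-sided: (1.645 + 1.405) / (1.645 + 0.468) = 3.050 / 2.113 = 1.44.
- Rounding of the published powers stretches these at most to about 1.41 and 1.47.

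A common design effect cancels from the ratio of the two z-values. For control rates of 10-50%, with the risk difference, log relative risk and log odds ratio as test scales, that ratio is about 1.60-1.74 if 1.3 and 1.5 are relative risks and about 1.53-1.59 if they are odds ratios. As a simple marker, ln 1.5 / ln 1.3 = 1.545. The required ratio is not reached.

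A search with effective sample size and control rate (10-50%) both left free came no closer than 63.9% and 96.1% (two-sided) or 65.2% and 94.8% (one-sided).

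**Step 2: which figure reproduces, and under what reading?**

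- Design effect: 1 + 9 × 0.06 = 1.54.
- Correlation of SME means across periods: r = 10 × 0.06 × 0.875 / 1.54 = 0.341, so r² = 0.116.
- Baseline-adjusted inflation: 1.54 × (1 − 0.116) = 1.361.
- Effective n per arm: 330 / 1.361 = 242.
- 39% v 30%: z = 2.09 (risk difference) or 2.07 (log relative risk).
- 45% v 30%: z = 3.45 or 3.35.

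| Specification | 50% arm | 100% arm | Stated figure matched |
|---|---|---|---|
| Stated in the article | 68% | 92% | |
| Two-sided, 33 v 33, baseline-adjusted | 54-55% | 92-93% | 92% only |
| One-sided, 33 v 33, baseline-adjusted | 66-67% | 96% | 68%, nearly |
| Two-sided, 33 v 33, follow-up only | about 50% | about 90% | neither |
| Two-sided, 33 v 66 (controls pooled), baseline-adjusted | 67-70% | 98% | 68% only |
| Two-sided, 33 v 33, clustering ignored | about 68% | about 98% | 68% only |
| Two-sided, 33 v 33, baseline-adjusted, effects as odds ratios | about 27% | about 56% | neither |

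The pooled row treats all 66 control SMEs as having a baseline, although the Participant timeline section gives one control arm none, so it is a favourable version. No row gives both stated figures.

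**The case against.** The strongest objection is that the documents do not show which figure is wrong. A reader might infer that the 50% arm really has 54-55% power and is close to a coin-flip. That holds only for a two-sided test, and sidedness is not stated. The classical figures are set beside a directional criterion (95% posterior probability that the effect exceeds 1). With the very weak analysis priors, its nearest frequentist counterpart is a one-sided 5% test. On that reading 68% is right to within one or two points and 92% is the odd figure. Pooling the control arms or ignoring clustering also gives about 68%, so no single slip can be named as the source. This objection stands.

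A second objection is that the cited method source and the additional files are not at hand, so formula and arms compared are assumptions. The ratio is also not strictly constant for every formula: holding the between-SME coefficient of variation fixed makes it depend on the clustering. That variant, baseline-adjusted at 33 v 33, gives about 50% and 88% two-sided, or 62% and 93% one-sided. The objection limits confidence in any one replacement value. It does not rescue the pair, because that variant also fails to give both figures.

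A third objection is that the 132 SMEs are justified by the assurance results, and the section itself says statistical significance is not the appropriate consideration. This also stands, and it limits the consequence.

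**Conclusion.** The pair is wrong as written: no specification tried gives both 68% and 92%, and the mismatch does not depend on sidedness or use of baseline data. At least one figure must change.

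The size of the error depends on what was intended. At 33 v 33 SMEs, baseline-adjusted, on the relative-risk scale, 68% is about 13 points too high if the test is two-sided, and 92% is about 4 points too low if it is one-sided. These sizes assume mid-range parameter values, normal approximations and the repeated cross-sectional variance formula shown above.

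The documents do not support going further, to the conclusion that the lower-incentive arm is underpowered or that the trial needs more SMEs. The sentence is a comparison with the assurance figures, which this check does not test. The point is a correction to a published number, of moderate weight.

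**What to change.** Restate the comparison sentence from one specification. Give sidedness, effect scale (relative risk or odds ratio), the arms compared (33 v 33, or both control arms pooled) and whether baseline data are used, and report both powers from it. Possible wordings, depending on what was intended:

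- Two-sided: 54% and 92%, two-sided 5%, log relative risk, 33 v 33 SMEs, baseline-adjusted.
- One-sided: about 66% and 96%, with the same other settings.
- Controls pooled, two-sided: about 67-70% and 98%, with a note on how the control arm without a baseline is handled.

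The authors should rerun their own calculation before choosing, since replacing 68% on an assumed sidedness could remove a correct figure. The cost is one sentence, with no change to the number of SMEs, the design or the analysis. If the test was two-sided, the stated power for the 50% arm becomes less favourable, and the text should then not leave the impression that it matches the 70% assurance.
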